#### Data Categorization

Socio-demographic and economic variables will be analyzed:

- - sex, age, ethnicity/color, origin, marital status, monthly income, education.

Pharmacotherapeutic variables will be analyzed:

- - prescription drugs classified according to the Anatomical Therapeutic Chemical Classification (ATC)[12] for UC and comorbidities, at levels 3 and

5. This variable will be collected at Time 0 and if there is a change in treatment;

- - therapeutic regimens for UC. This variable will be collected at Time 0 and if there are changes in treatment;
  - self-reported drug non-adherence for drugs being treated for UC, according to MGLT[8]. This variable will be collected at Time 0 and 6 months;
  - number of educational interventions of the “Drug Guidance” type: frequency of guidance per drug per patient carried out during the intervention program;
  - number of behavioral interventions of the “Therapeutic Scheme” type: frequency of therapeutic schemes per patient performed during the intervention program;
  - number of behavioral interventions of the “Pharmaceutical Guidance Table” type: frequency of the table per therapeutic regimen per patient, performed during the intervention program;
  - number of behavioral interventions of the type “SMS Reminder Type”: frequency of SMS reminder type per patient, performed during the duration of the intervention program;

Clinical variables will be analyzed:

- - disease activity - Lichtiger index[9], which establishes the clinical status of UC. This variable will be collected at Time 0 and 6 months;

Subjective variables reported by the patient will be analyzed (Patient Reported Outcomes - PRO):

- - quality of life. This variable will be collected at Time 0 and 6 months using the Brazil SF-36 questionnaire[53];

#### Sample Calculation

We will consider a bilateral significance level (1-alpha) of 95%, power (1-beta) with 80% probability of detection, sample size ratio between exposed/unexposed of 1, percentage of positive unexposed of 50%[13] and percentage of positive exposure of 80%, Odds Ratio: 4, risk/prevalence ratio of 1.6 and risk/prevalence difference of 30, the calculation generated through OpenEpi, version 3.01, calculated 45 participants in each group (CG and IG) for UC patients, with a sample size of 90.

#### Statiscal Analysis

Quantitative variables (age, disease duration, UC severity score, for example) will be described as means (standard deviation) or medians (interquartile range), while qualitative variables (gender, marital status, education, for example) will be described with absolute and percentage frequency measures. To compare exposed (GI) and non- exposed (CG) groups in relation to qualitative variables, the chi-square test or Fisher's exact test will be used, when recommended. The comparison of quantitative variables between exposure groups will be performed by applying Student's t test for unpaired samples or, if indicated, the nonparametric Mann-Whitney test.

The occurrence (incidence) of the study outcomes (non-adherence) will be performed by the ratio between the total number of participants who did not adhere to the treatment and the total number of participants in the group, multiplied by 100, calculated separately for the intervention and comparative groups. The relative risk (RR) with the respective 95% confidence interval (95%CI) will be used as a measure of efficacy, obtained by the ratio between the incidence of the intervention group and the incidence of the comparative group. For adjustments for potential confounders, Poisson regression with robust variance will be used to estimate adjusted RR with the respective 95%CI. Associations with p values lower than 0.05 will be considered significant.

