#### SPECIFIC AIMS

1. To assess possible factors associated with the impact of an intervention program on non-adherence to drug treatment in patients with UC;
2. To evaluate the impact of an intervention program on the quality of life of patients with UC.

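### Quality of life is a stated aim and SF-36 is measured at Time 0 and 6 months, but the only between-group test named makes no stated use of the Time 0 score, which costs precision

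*Protocol*

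**What the plan says.** The second of the two specific aims in the Protocol is "To evaluate the impact of an intervention program on the quality of life of patients with UC". Under Data Categorization, the entry for quality of life says "This variable will be collected at Time 0 and 6 months using the Brazil SF-36 questionnaire". The Lichtiger index of disease activity is collected at the same two times but appears in no stated aim.

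The Statistical Analysis section has one sentence on comparing such scores between arms: "The comparison of quantitative variables between exposure groups will be performed by applying" an unpaired Student's t test or, where indicated, the Mann-Whitney test. The UC severity score is among its examples of quantitative variables. The section mentions no change score, no baseline covariate and no other use of the Time 0 value. The only adjustment it plans is Poisson regression with robust variance. That yields an adjusted relative risk for non-adherence, which is binary, so it does not reach the SF-36 or Lichtiger scores.

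**The concern.** When a score is measured before and after randomised treatment, its baseline value usually explains part of the variation at follow-up. A two-sample test of the 6-month score leaves that part in the error term. The confidence interval is then wider than it need be, and in the one trial that is run, a chance difference between arms at Time 0 shows up partly as an apparent difference at 6 months.

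This matters here because the 90 participants were sized for non-adherence alone. Nothing was sized for quality of life, so the precision available for Aim 2 is whatever 45 per group happens to give. The Protocol names the test for quantitative variables, and a later analysis plan that follows the text would inherit it.

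**Working it through.** **Plan's own figure.** The Sample Calculation section assumes a "bilateral significance level (1-alpha) of 95%, power (1-beta) with 80% probability of detection", a 1:1 ratio, 50% in the unexposed and 80% in the exposed.

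- Uncorrected: n = [1.960 × √(2 × 0.65 × 0.35) + 0.842 × √(0.5 × 0.5 + 0.8 × 0.2)]² / 0.30² = 38.5, so 39 per group.
- With the Fleiss continuity correction: n = (38.5 / 4) × [1 + √(1 + 4 / (38.5 × 0.30))]² = 44.9, so 45 per group.

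This reproduces the stated result: "calculated 45 participants in each group (CG and IG) for UC patients, with a sample size of 90". The sample size is not in dispute. It only supplies n for what follows.

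**Inputs for quality of life.** From the Protocol: n = 45 per group and two-sided 5%. Assumed, because the Protocol gives none of them: a correlation r between Time 0 and 6 months of 0.3 to 0.7, a true difference of 0.5 SD, and no dropout.

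**Formulas, relative to a t test on the 6-month score.**

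- ANCOVA: variance ratio 1 − r², equivalent to 45 / (1 − r²) patients per group analysed without baseline.
- t test on change from Time 0: variance ratio 2(1 − r).
- Power: noncentral t with noncentrality 0.5 / [√(1 − r²) × √(2/45)]. Without baseline this is 0.5 / 0.211 = 2.37.

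| Analysis | Variance ratio | Equivalent n per group | Power for 0.5 SD | Difference with 80% power |
|---|---|---|---|---|
| t test on 6-month score | 1.00 | 45 | 65% | 0.60 SD |
| ANCOVA, r = 0.3 | 0.91 | 49 | 69% | 0.57 SD |
| ANCOVA, r = 0.5 | 0.75 | 60 | 77% | 0.52 SD |
| ANCOVA, r = 0.7 | 0.51 | 88 | 91% | 0.43 SD |

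A normal approximation gives powers of 66%, 70%, 78% and 91%, so the method of calculation matters by about one point at most.

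**Chance imbalance.** The difference in Time 0 means between two groups of 45 has standard error √(2/45) = 0.21 SD, so its 95% range is about ±0.41 SD. An unadjusted 6-month comparison carries r times the realised imbalance. At the edge of that range this is 0.3 × 0.41 = 0.12 SD, 0.5 × 0.41 = 0.21 SD and 0.7 × 0.41 = 0.29 SD.

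**If the t test were applied to change.** The variance ratio is 1.4 at r = 0.3, 1.0 at r = 0.5 and 0.6 at r = 0.7. Change is worse than the plain 6-month comparison below r = 0.5. It is worse than ANCOVA at every r below 1, because 2(1 − r) − (1 − r²) = (1 − r)², which is positive.

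**The case against.** The sentence on quantitative variables names neither SF-36 nor the 6-month visit. Most of the examples around it are entry characteristics such as age and education, and the outcome analysis of non-adherence starts in the next paragraph. It could therefore be read as a rule for comparing the groups at entry, with the SF-36 model left to an analysis plan that is not at hand. Even if it covers SF-36, it does not say whether the test is on the 6-month score or on change. This stands as a reason not to say that the plan rules out any use of baseline. It does not remove the point: no other method for Aim 2 is given, the severity score is listed under this rule, and the change-score reading is still less precise than ANCOVA.

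A reader might infer that the planned comparison is biased. The documents do not support that. Allocation is randomised, so the unpaired test is unbiased on average and its confidence interval already allows for chance imbalance. The loss is in precision.

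The gain also depends on r. The Protocol's own video text describes these diseases as moving between crises and remission, so a low correlation over 6 months is plausible, and at r = 0.3 the variance falls by only 9%.

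It is tempting to extend the point to the primary relative risk, by requiring the baseline Morisky-Green-Levine score and the clinic as covariates. The document gives no basis for calling that score the strongest predictor, and it describes no stratification by clinic. An adjusted relative risk is already planned, and the choice of its covariates can be left to the analysis plan.

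**Conclusion.** The point holds as one of efficiency on a non-primary aim. For quality of life, the only between-group method stated makes no declared use of a baseline that the trial collects from every participant. For r between 0.3 and 0.7, ANCOVA removes 9% to 49% of the variance. At 45 per group it lifts power for a 0.5 SD difference from about 65% to between 69% and 91%. Both r and the 0.5 SD are assumptions, and so is complete follow-up.

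The sample size and the primary relative risk are untouched, and the named test remains valid. The point weighs less for the Lichtiger total, which belongs to no stated aim. It is worth acting on because the gain is free. It is no ground for calling the plan unsound.

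**What to change.** In the Statistical Analysis section, add that each SF-36 domain is compared between groups by ANCOVA of the 6-month score on group and Time 0 score, reporting the adjusted mean difference with its 95% CI. Apply the same model to the Lichtiger total as a secondary clinical variable. That total is bounded (0 to 21 from the item scores on the form), so keep the unpaired t test or Mann-Whitney test as a check, or for use where the distribution is unsuitable for a linear model.

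The cost is a few sentences of Protocol and analysis-plan wording. Both scores are already on the initial and final questionnaires, so no new data, visit or participant is needed.

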#### Exclusion Criteria

Patients who do not meet the research criteria will be excluded, as well as patients who are classified as adherent during the recruitment stage.

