#### Data Collection

Data collection will be carried out by a team of scientific initiation scholarship holders, duly trained and qualified, under the guidance of the other researchers, including the course of Good Clinical Practices through a web platform (https://gcp.nidatraining.org/). We will use the semi-structured interview technique with questionnaires designed specifically for this study for initial data collection, prior to the proposed intervention program (Appendix 3), and at the end after 6 months of the

intervention program (Appendix 4). Validated instruments for the Brazilian reality will be used, such as the Brasil SF-36[7], which captures the participants' quality of life and the Morisky-Green-Levine Test (MGLT)[8] to measure the degree of non-adherence, as well as the Lichtiger Index[9] to determine the clinical activity of UC. We will also collect secondary data from the participants' medical records, when necessary. A form will be used to record the interventions carried out that will make up the intervention program (Appendix 5). The data will be entered in a database built with the SPSS® statistical package, version 21.0.

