**ADHERENCE DATA: MORISKY-GREEN-LEVINE TEST (MGLT)**

**Instructions**: mark below with an “X” according to the treatment for UC

|  |  | **YES** | **NO** |
| --- | --- | --- | --- |
| **NON INTENTIONAL** | 1. Do you ever forget to talke your medicine? |  |  |
|  | 2. Are you careless at times about taking your medicine? |  |  |
| **INTENTIONAL** | 3. When you feel better do you sometimes stop taking your medicine? |  |  |
|  | 4. Sometimes if you feel worse when you take the medicine, do you stop taking it? |  |  |

1. According to MGLT, classify:
   1. Adherent, if answered NO to ALL questions
   2. Moderate adherence, if answered YES to 1 or 2 questions
   3. Low adherence, if answered YES to 3 or 4 questions

(9) NA

1. Non-adherence tipology according to MGLT: (1) Intentional (2) Non-intentional (3) Both (9) NA

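### The MGLT is graded at both visits, but the only stated efficacy analysis is a yes/no relative risk that does not specify use of entry severity and, on the natural cut-off, does not register partial improvement

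*Protocol*

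**What the plan says.** - **Instrument.** Protocol, Data Collection, uses the MGLT "to measure the degree of non-adherence". Appendices 3 and 4 record the same four YES/NO items at entry and at 6 months. Both grade the result: NO to all items is adherent, then "Moderate adherence, if answered YES to 1 or 2 questions", then low adherence for three or four YES.
- **Entry rule.** Exclusion Criteria removes patients who do not meet the criteria, "as well as patients who are classified as adherent during the recruitment stage". Everyone randomised is therefore non-adherent at Time 0.
- **Efficacy analysis.** Statistical Analysis defines the outcome in each arm as "the ratio between the total number of participants who did not adhere to the treatment and the total number of participants in the group", times 100, and compares arms by the RR. A robust Poisson model adjusts for potential confounders, none of which is named. No analysis of the MGLT grades or of the number of YES answers is named.
- **Aim and sizing.** The general aim concerns a rate of non-adherence, and Sample Calculation is a comparison of two percentages.

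**The concern.** With everyone non-adherent at entry, the yes/no baseline is a constant and cannot be used for adjustment. What does vary at entry is severity, from 1 to 4 YES, and the plan does not commit to using it. A patient with 1 YES at entry needs one answer to change to become adherent; a patient with 4 YES needs four. In a trial of 90, a chance difference in severity between arms feeds into an RR that ignores it.

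At follow-up, only the all-NO class carries the label adherent. If any YES therefore counts as non-adherent, a patient who goes from four YES (low) to one YES (moderate) is scored like a patient who did not change, although the protocol itself separates the two grades. At stake are some power, protection against imbalance, and the ability to describe partial benefit from an analysis fixed in advance rather than added after the results are known.

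**Working it through.** **1. The plan's own sample size.** Inputs from Sample Calculation: "bilateral significance level (1-alpha) of 95"%, "power (1-beta) with 80% probability of detection", "sample size ratio between exposed/unexposed of 1", "percentage of positive unexposed of 50"%, and 80% among the exposed. The word positive is not defined; I read it as adherent, so non-adherence is 50% vs 20%. The formula gives the same n either way.

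- Uncorrected: n = [1.960·√(2·0.65·0.35) + 0.842·√(0.25 + 0.16)]² / 0.30² = (1.322 + 0.539)² / 0.09 = 38.5, so 39 per arm.
- With continuity correction: n' = (38.5/4)·[1 + √(1 + 4/(38.5·0.30))]² = 44.9, so 45 per arm.

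The stated 45 per group reproduces, and it is a calculation for a binary outcome.

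**2. Binary against graded outcome, ignoring baseline.** The protocol gives no distribution of MGLT scores, so the splits are assumptions. Proportional-odds sample size (Whitehead), with p̄ the category proportions averaged over arms:

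N = 12(1.960 + 0.842)² / [(ln OR)²(1 − Σp̄³)], with OR = 4, so N ≈ 49.0 / (1 − Σp̄³).

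- Binary, 50% vs 80% adherent: Σp̄³ = 0.65³ + 0.35³ = 0.3175; N = 49.0/0.6825 = 71.8, or 35.9 per arm.
- YES count 0-4, control split 50/20/15/10/5%: Σp̄³ ≈ 0.279; N ≈ 68.0, or 34.0 per arm.
- Relative efficiency of binary = 34.0/35.9 ≈ 0.95. Over the splits tried it is 94-97%.
- With lower control adherence at 6 months it is 85-92% (at 30% adherent), 74-86% (at 20%) and 53-72% (at 10%).
- Extreme case: adherence equal at 50% in both arms, low grade 40% vs 10%. Simulated power at 45 per arm is 27% for the ordinal test and 5% for the binary one.

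**3. Adding the Time 0 count.** Simulation, 45 per arm: four yes/no items driven by a personal tendency (SD 1.2) with logistic noise; correlation of that tendency between visits 0.5 to 0.7; entry only with at least 1 YES. Ranges cover repeated runs and both correlations. With 600 trials in a run, the Monte Carlo standard error is at most √(0.5·0.5/600) = 2 points.

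| Non-adherence, control vs intervention | RR, unadjusted Poisson | RR, entry count added | YES count, adjusted for entry count |
|---|---|---|---|
| near the planned 50% vs 20% | 85-87% | 86-89% | 92-95% |
| about 72% vs 50% | 55-59% | 57-63% | 76-83% |
| 48% vs 27.5% | 46-50% | not tabulated | 63-65% |

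Rejection rates under no effect were about 3-7%. Compared within runs, the adjusted count gains about 6 to 8 points near the planned rates and about 20 points at 72% vs 50%. The entry count in the Poisson model gains about 2 to 6 points; some runs gave as little as 1.

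**4. Imbalance in severity.** In the same model, control non-adherence at 6 months rises from 59-62% for 1 YES at entry to 82-87% for 4 YES. Taking midpoints (60.5% and 84.5%), if five of 45 patients in one arm had 4 YES instead of 1, that arm's rate moves by 5/45 × 24 = 2.7 points. On a base of 72% this alone gives RR = 74.7/72 = 1.04. The effect is small but avoidable.

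**The case against.** The strongest reply is that the plan is coherent. The aim is a rate, the sizing is for two proportions, entry requires non-adherence, and the analysis is a proportion. Describing the MGLT as measuring degree says what the instrument does; it does not promise a graded endpoint. All of that stands.

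A reader might infer that most of the instrument's information is discarded. The figures do not support that: at the planned rates the binary outcome keeps about 94-97% of unadjusted ordinal efficiency, and it keeps more than half even at 10% control adherence in the splits tried. A reader might also infer that a program with partial benefit would be reported as having no impact. That needs an effect which moves patients from low to moderate while hardly moving anyone to zero YES. In the item model the same treatment shift also lowers the binary rate, from about 72% to 50%. Nor does the protocol state that such a patient counts as unchanged; this follows only if any YES is non-adherent, a cut-off that Statistical Analysis leaves unstated.

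Finally, covariates and supportive analyses often sit in a statistical analysis plan, the Poisson model does not exclude the entry count, and the chi-square or Fisher tests could be applied to the three grades. This is fair and limits the point. What remains is that the protocol fixes its efficacy measure here without saying which grades it counts, while its entry rule leaves severity as the only usable baseline adherence information.

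**Conclusion.** The point holds as an improvement to the analysis, not as an error in the primary outcome. The RR is the right headline for this aim and sample size, and near the planned effect its simulated power (85-87%) exceeds the 80% target. The unused information matters more if the effect is smaller than planned or if few controls become adherent. The latter is plausible, since controls start at 0% adherent and receive no program, but the protocol gives no figure for it.

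The power gains rest on an assumed item structure and assumed rates, and the efficiency figures on proportional odds. They show the order of size, not precise values. The undefined cut-off and the absence of a commitment to entry severity can be read directly from the text and do not depend on any model.

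**What to change.** In Statistical Analysis:

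1. Keep the RR of non-adherence at 6 months as the primary measure, and state that non-adherent means at least 1 YES on the MGLT, matching the entry rule.
2. Name the Time 0 YES count (1-4) as a fixed covariate in the robust Poisson model.
3. Prespecify one analysis, labelled supportive: the 6-month YES count (0-4) compared between arms with adjustment for the Time 0 count, by a proportional-odds or linear model. Report the shift across the three MGLT grades by arm.

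The cost is wording only. All four items are already recorded at both visits, and the sample size does not change. The downside is one extra result, which must be labelled so that it cannot stand in for the primary RR.

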**Appendice 2 – Research Protocol Flowchart**

[figure not shown]

#### Appendice 3 – Survey Questionnaire for initial data collection

- 1. Participant identification code: | | | | |
  2. Date (time 0): / /
  3. Interviewer:

**SOCIO-DEMOGRAPHIC DATA**

- 1. Procedence: (1) Countryside (2) Urban (9) Not applicable (NA)
  2. Sexo: (1) masculino (2) feminino (9) NA
  3. Birth date: / /
  4. Age (Years): ( )
  5. Ethnicity/collor (self-declared): (1) black (2) white (3) mixed race (4) yellow (5) indigenous

(6) no declaration. (9) NA

- 1. Children: (1)one (2)two (3)three or more (9)NA
  2. Religion: (1)Catholic (2)Evangelic (3)Spiritualist (4) No religion (9)NA
  3. Marital status: (1) Single (2) Married (3) Divorced (4) Widow(er) (9) NA
  4. Education: (1) Incomplete primary school (2) Complete primary school (3) Incomplete highschool

(4) Complete highschool (5) Incomplete university (6) Complete university (9) NA.

- 1. Family income (minimum wage): (1) no income, up to 1 (2) more than 1, up to 2 (3) more than 2,

up to 3 (4) more than 3, up to 5 (5) more than 5, up to 10 (6) more than 10, up to 20 (7) more

than 20 (8) NA

**QUALITY OF LIFE DATA (BRASIL SF 36)**

**Instructions**: this survey asks you about your health. This information will keep us informed of how you feel and how well you are able to carry out your activities of daily living. Answer each question by marking the answer as indicated. If you are unsure how to respond, please try to answer as best you can.

[figure not shown]

[figure not shown]

[figure not shown]

[figure not shown]

[figure not shown]

**ADHERENCE DATA: MORISKY-GREEN-LEVINE TEST (MGLT)**

**Instructions**: mark below with an “X” according to the treatment for UC

|  |  | **YES** | **NO** |
| --- | --- | --- | --- |
| **NON INTENTIONAL** | 1. Do you ever forget to talke your medicine? |  |  |
|  | 2. Are you careless at times about taking your medicine? |  |  |
| **INTENTIONAL** | 3. When you feel better do you sometimes stop taking your medicine? |  |  |
|  | 4. Sometimes if you feel worse when you take the medicine, do you stop taking it? |  |  |

1. According to MGLT, classify:
   1. Adherent, if answered NO to ALL questions
   2. Moderate adherence, if answered YES to 1 or 2 questions
   3. Low adherence, if answered YES to 3 or 4 questions

(9) NA

1. Non-adherence tipology according to MGLT: (1) Intentional (2) Non-intentional (3) Both (9) NA

